### Ethical approval

Full ethical approval has been granted by the National Research Ethics Service (NRES) East Midlands – Nottingham 2 research ethics committee (REC) (reference 14/EM/1305).

### Screening, eligibility and patient pathway

Screening will be conducted by research nurses, who will also identify potential participants, gain informed consent and conduct a baseline assessment. Patients will be recruited from hospital and community-based ulcer clinics, and through liaison with general practitioners (GPs), community nurses and hospital staff. Eligibility will be confirmed by a doctor. The participant will continue with regular (usually weekly or 2-weekly) visits to the usual place of ulcer care, where the research or treating nurse will assess the components involved in the study. An additional file shows a summary of AVURT assessments (see Additional file 3).

### Inclusion criteria

Inclusion criteria are:Patients with at least one chronic venous leg ulcer (if more than one ulcer, the largest ulcer will be chosen as the reference ulcer for the purposes of the trial)Ulcer area > 1 cm^2^ABPI ≥ 0.8 taken within the previous three months, *or*if the ABPI is incompressible, other forms of clinical assessment must exclude peripheral arterial disease (peripheral pulse examination, toe pressure, Duplex ultrasound, clinical judgement)Age over 18 years (no upper age limit)

## Informed consent

### Exclusion criteria

The exclusion criteria are:Unable to provide consentUnwilling to provide consentFoot ulcer (i.e. below the ankle)Leg ulcer of non-venous aetiologyABPI < 0.8 or, where ABPI is not compressible, peripheral arterial disease (PAD) cannot be excluded by other assessmentsRegular concomitant aspirinPrevious intolerance or contraindication to aspirin use (according to prescriber’s clinical judgement)Prohibited medication: probenecid; oral anticoagulants including coumarins (warfarin, acenocoumarol) and phenindione; dabigatran; rivaroxaban; apixiban; heparin; clopidogrel; dipyridamole; sulfinpyrazone and iloprostKnown lactose intolerancePregnant/lactating womenMale or pre-menopausal female participants of child-bearing potential^1^ unwilling to use an effective method of birth control (either hormonal in the form of the contraceptive pill or barrier method of birth control accompanied by the use of a proprietary spermicidal foam/gel or film; or agreement of true abstinence (i.e. withdrawal, calendar, ovulation, symptothermal and post ovulation are not acceptable methods) from time of consent is signed until 6 weeks after the last dose of Investigational Medicinal Product (IMP)Already participating in another study investigating leg ulcer therapyPreviously been recruited into this trialAnother reason that excludes them from participating within this trial (decision made according to the nurses’ or prescribers’ clinical judgment)

There will be no exceptions (waivers) to eligibility criteria. Participants will be considered eligible if they meet all of the inclusion criteria and none of the exclusion criteria mentioned above. Details of all screened patients, whether recruited or not, will be entered onto the sponsor screening log.

### Consent

The process of consent will be carried out in accordance with the Declaration of Helsinki. All patients will be fully informed about the nature of the research study and the chances of being randomised to either the trial drug (aspirin) or placebo. Written information will be provided to patients, who will have the opportunity to discuss the study with a member of the trial team prior to enrolment in the study. Patients will be aware that their decision to participate in the study is voluntary and that they are free to withdraw consent at any time with no effect on the standard treatment they receive. Written consent forms will be obtained from patients willing to participate in the study and will be retained by the investigator.

### Randomisation and blinding

Participants will be randomised on a 1:1 basis to receive either aspirin (300 mg) or placebo, in addition to standard care. The Research Pharmacy responsible for dispensing all trial medication (St George’s Hospital) will receive a randomisation schedule generated in advance by the IMP manufacturer, Sharp Clinical Services UK Ltd. (Sharp Clinical Services, UK) Stratification will be by ulcer size (≤5 cm^2^ or > 5 cm^2^).

Randomisation will be performed by the Research Pharmacy upon receipt of a valid prescription for a participant. Researchers, treating staff, clinicians and participants will be blind to treatment allocation. A 24-hour code-breaking service will be provided by the Research Pharmacy in case of requirement for emergency unblinding and participants will receive a study-specific 24-hour emergency contact card.

### Sample size calculation

This study aims to recruit 100 patients, which is sufficient to demonstrate whether there is evidence for efficacy of aspirin to treat VLUs, in line with previous similar trials [23, 24] and is also large enough to test the feasibility of study procedures such as recruitment.

The primary outcome is time to healing of the reference ulcer. Applying an assumed standard error for the hazard ratio (HR) of 0.105 following adjustment for log area and log duration of ulcer (as in VenUS IV) to the smaller sample size in this study implies that the standard error would be 0.22. A 95 % confidence interval (CI) for the log hazard ratio would thus be log(HR) ± 0.435. Hence, if the hazard ratio for this study were the same as that suggested by previous studies (around 1.5), the confidence interval would be (0.97, 2.31) which just includes 1.00. To further increase the power an IPD meta-analysis is proposed. As compliance and follow-up will be measured as part of the study there is no formal inflation for dropout.

An important secondary outcome is wound area. Assuming a standard deviation of 1.09 following log transformation as in (VenUS I) [15], 2 groups of 50 participants will render 80 % power to detect a difference of 0.62 on the natural log scale. This corresponds to a reduction of 46 % in ulcer area at follow-up. In the current study, there will be multiple measurements of wound area and so smaller differences should be detectable.

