### Aspirin

Aspirin is a cyclooxygenase inhibitor that irreversibly reduces prostaglandin-2 and thromboxane A2, which are involved in inflammation and platelet aggregation [21]. It is inexpensive, widely used and readily available. The mechanism by which aspirin may hasten healing of VLUs is unclear but may be associated with a reduction of inflammation, or its effect on the microvascular circulation, including platelet activation. In one study investigating the haemostatic effects of aspirin in patients with VLU, the investigators demonstrated that participants were found to have increased levels of fibrinogen and shortened coagulation rate, when compared to age-matched and sex-matched controls and that treatment with aspirin caused prolongation of the coagulation rate, which increased the rate of ulcer healing [22].

There have been 2 small randomised trials to date that have investigated the use of aspirin (300 mg) in VLUs; however, the quality of evidence presented was low and more robust studies are required to confirm their findings. An additional file outlines the previous studies investigating aspirin in VLUs (see Additional file 1).

The first study was carried out in 1994 and demonstrated that 38 % more patients healed in the treatment group (aspirin plus compression) than in the control group (placebo plus compression) [23]; however, no patients healed within 4 months in the control group, which is surprising, given that the median time to healing with compression alone is around 3 months [15]. Although it provides some limited data about the potential use of aspirin therapy, the sample size of only 20 patients is insufficient to draw meaningful conclusions. In addition, patients were only followed-up for 4 months.

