### Statistical analysis

Analyses will be in accordance with the principles of intention-to-treat. Analysis will be conducted in Stata® (Stata Corporation, College Station, TX, USA) or similar statistical software. Statistical significance will be assessed at the 2-sided 5 % level unless otherwise stated. Ninety-five percent CIs will be provided as appropriate. Statistical analyses will be detailed in an analysis plan that will be independently reviewed and agreed before data are analysed.

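### The claim that 100 patients is sufficient to show efficacy conflicts with the plan's own confidence interval, which implies about 45 % power at a hazard ratio of 1.5

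*Protocol article*

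**What the plan says.** The section Sample size calculation opens with the claim "This study aims to recruit 100 patients, which is sufficient to demonstrate whether there is evidence for efficacy of aspirin to treat VLUs". It adds that the number is comparable with earlier trials and large enough to test study procedures.

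The second paragraph turns to the primary endpoint: "The primary outcome is time to healing of the reference ulcer". Its starting point is a figure from an earlier trial: "Applying an assumed standard error for the hazard ratio (HR) of 0.105 following adjustment for log area and log duration of ulcer". Applying this "to the smaller sample size in this study implies that the standard error would be 0.22". The half-width of the 95 % interval for the log hazard ratio is printed as 0.435. At the value attributed to previous studies, about 1.5, "the confidence interval would be (0.97, 2.31) which just includes 1.00". A pooled individual patient data analysis is proposed to raise power, and no allowance is made for dropout.

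The only power printed in the section is 80 %, for the secondary outcome of wound area. The section Statistical analysis sets the test level: "Statistical significance will be assessed at the 2-sided 5 % level unless otherwise stated". The Abstract makes efficacy the primary objective and places feasibility and safety among the secondary ones.

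**The concern.** Two adjacent paragraphs cannot both stand. The first says the trial is large enough to settle whether there is evidence of efficacy. The second shows that if the trial observed exactly the effect suggested by earlier work, the 95 % interval would still contain 1, so the result would not be significant at the level the protocol sets.

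The description of the interval as only just including 1 sounds like a near miss. An interval that includes 1 when the estimate equals the true value means that the chance of significance is below one half. A reader who sees an unqualified claim of sufficiency, and 80 % as the only printed power, could conclude that the primary comparison is well powered. If aspirin works as supposed, a non-significant result is the more likely outcome, and a prior statement that the size was sufficient makes such a result easier to misread as evidence of no effect.

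**Working it through.** **Inputs.** All come from the protocol article.

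- Sample size calculation: 100 patients; standard error (SE) of the log hazard ratio 0.22; printed half-width 0.435; hazard ratio (HR) about 1.5.
- Statistical analysis: two-sided 5 % level, so the critical value is 1.960.
- Randomisation and blinding: 1:1 allocation.

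The size of the earlier trial that supplied the 0.105 is not given, so the projected 0.22 is taken as stated.

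**Step 1: reproduce the printed interval.** ln(1.5) = 0.4055 and 1.960 × 0.22 = 0.4312.

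- Lower limit: exp(0.4055 − 0.4312) = 0.975.
- Upper limit: exp(0.4055 + 0.4312) = 2.309.

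This matches the printed (0.97, 2.31). The printed 0.435 corresponds to SE = 0.435/1.960 = 0.222 and an interval of (0.971, 2.317). The difference is rounding.

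**Step 2: test statistic if the observed HR is 1.5.** z = 0.4055/0.22 = 1.84, two-sided p = 0.065. This is not significant at 5 %.

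**Step 3: power if the true HR is 1.5.** Power = Φ(ln(HR)/SE − 1.960).

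| SE | Source | Power |
|---|---|---|
| 0.215 | lower rounding limit of 0.22 | 47.0 % |
| 0.220 | as printed | 45.3 % |
| 0.222 | implied by half-width 0.435 | 44.7 % |
| 0.225 | upper rounding limit of 0.22 | 43.7 % |

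At the printed SE, the chance of a non-significant result is 100 − 45.3 = 54.7 %, about 55 %.

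**Step 4: HR at which power is conventional.** HR = exp((1.960 + z_power) × 0.22).

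- 80 % power: exp((1.960 + 0.842) × 0.22) = 1.85.
- 90 % power: exp((1.960 + 1.282) × 0.22) = 2.04.

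**Step 5: cross-check through events.** With 1:1 allocation, SE² ≈ 4/events, so events ≈ 4/0.22² = 82.6, about 83. Schoenfeld's formula with 83 events and HR 1.5 gives 45.5 %. Even if all 100 ulcers healed, power would be about 53 %. The Background says more than a quarter of ulcers fail to heal. As an illustration, 75 events would give about 42 %.

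**Step 6: precision.** exp(0.431) = 1.54, so the 95 % interval runs from the estimate divided by about 1.5 to the estimate multiplied by about 1.5.

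**The case against.** The best defence is that nothing is hidden or miscalculated. Every printed figure in the primary-outcome paragraph reproduces, no power is claimed for that outcome, and the authors themselves say that the interval includes 1 and propose a pooled analysis. The section Trial design says the study is meant to inform the feasibility of a larger confirmatory trial, and 100 patients may be a sound number for that. The HR of 1.5 enters conditionally, as the value seen before.

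Most of this stands, and it reduces the severity. It does not rescue the word sufficient. The sentence claims efficacy as well as feasibility, for this trial alone and not for the pooled analysis, while the Abstract makes efficacy the primary objective.

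Some stronger readings are tempting but not supported:

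- *That 1.5 is the planned, adjusted design effect, and that the second earlier trial undermines it.* The article does not call 1.5 a design target or an adjusted value. It reports no HR from that trial. Failure to be an independent predictor among 51 patients does not exclude an HR near 1.5. The source of the figure lies in papers not at hand.
- *That the Background dismisses both earlier trials as too small.* It says so of the first: "the sample size of only 20 patients is insufficient to draw meaningful conclusions". It describes the 51-patient trial as a small pilot, but its stated reservations there concern reporting of the placebo and uncertain effect estimates.
- *That a non-significant result would end the route to phase III.* The article ties no go or no-go decision to significance. Misinterpretation is a risk, not a stated consequence.

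**Conclusion.** The point holds as a contradiction between a claim and the figures that follow it. On the plan's own SE, an HR of 1.5 and a two-sided 5 % test, power for the primary comparison is about 45 % (44 % to 47 % over the rounding of the SE), and 80 % is reached only at an HR of about 1.85.

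The result rests on a normal approximation for the log HR and on the projected SE of 0.22 being achieved. That SE corresponds to roughly 83 healed ulcers among 100 patients. Fewer healing events would lower the power.

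The printed interval is correct, and it and the meta-analysis proposal disclose part of the shortfall. The finding concerns the sufficiency statement. It does not show that 100 patients is the wrong number for a phase II trial with a feasibility role.

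**What to change.** In Sample size calculation, replace the efficacy half of the opening sentence and keep the feasibility justification. The revised text should state four things:

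1. With an SE of 0.22 and a two-sided 5 % test, power is about 45 % at an HR of 1.5 and reaches 80 % only at about 1.85.
2. This trial alone estimates the HR with a 95 % interval of about a factor of 1.5 either way.
3. A non-significant result will not be read as absence of effect.
4. The planned individual patient data meta-analysis is needed for a firm conclusion on efficacy.

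The cost is a few sentences. Sample size, outcome and analysis do not change. The downside is a less favourable stated figure. The rewording carries most weight if it is made before results are known.

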## Background

Venous leg ulcers (VLUs) are wounds of the lower limb caused by a diseased venous system, typically occurring in the gaiter area of the leg. VLUs represent the most common cause of leg ulceration, with a lifetime prevalence of 1–3 % in UK adults and accounting for around 85 % of all lower limb ulcers [1].

Many VLUs take over 6 months to heal; one large study demonstrated a median time to ulcer healing of 99 days with 2-layer compression therapy [2]. In addition, more than a quarter fail to heal completely [3] and the 12-month recurrence rate of healed VLUs may be up to 28 % [4, 5]. Patients with longstanding, large ulcers, or who have a prior history of ulceration, are particularly resistant to healing [6, 7]. VLUs impair quality of life (QoL); they are open wounds, which can be large, are often painful, frequently become infected and leak exudate. Compression bandaging is an effective treatment [8] but requires the use of sometimes bulky bandages alongside the need for regular clinic visits. Health-related QoL is decreased in patients with VLUs, which can incur significant psychological morbidity [9], and successful treatment has been shown to significantly improve QoL [10]. VLUs represent a significant health economic burden, costing up to £1300 to treat 1 VLU episode for a year in the UK [11]. There is, therefore, an unmet need for a more cost-effective and clinically effective treatment for VLUs.

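### The standard error of 0.22 for the primary outcome is scaled by sample size alone, presupposes about 81 to 83 observed healings, and is mildly optimistic; the reason given for making no dropout allowance is invalid

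*Protocol article*

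**What the plan says.** All the precision figures for the primary outcome stand in one paragraph of the protocol article, under Sample size calculation.

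- The starting point is borrowed from VenUS IV: "Applying an assumed standard error for the hazard ratio (HR) of 0.105 following adjustment for log area and log duration of ulcer".
- It is applied "to the smaller sample size in this study implies that the standard error would be 0.22". Sample size is the only scaling factor named.
- The 95% interval for the log HR "would thus be log(HR) ± 0.435".
- The effect considered is put this way: "if the hazard ratio for this study were the same as that suggested by previous studies (around 1.5". For that case "the confidence interval would be (0.97, 2.31) which just includes 1.00".
- On losses: "As compliance and follow-up will be measured as part of the study there is no formal inflation for dropout".

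The Background section describes healing as follows: "Many VLUs take over 6 months to heal; one large study demonstrated a median time to ulcer healing of 99 days", and "more than a quarter fail to heal completely". Treatment period and follow-up sets 25 weeks from randomisation. Under Primary outcome, participants who withdraw, are lost or die unhealed are censored at that time.

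**The concern.** The variance of an estimated log HR is governed by the number of events, here healings. Rescaling another trial's SE by the ratio of sample sizes carries over that trial's proportion of participants with an observed healing. The article does not set that proportion against its own follow-up period or its own account of how fast these ulcers heal.

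The dropout sentence adds a faulty inference. A participant who leaves before healing contributes no event. Recording that this happened, or how well capsules were taken, does not put the event back.

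At stake is how precise the trial claims it will be. The SE, the half-width and the interval are the only precision figures given for the primary outcome, and they support the impression of an interval that narrowly misses excluding 1.

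**Working it through.** **Inputs from the article.** Source SE 0.105, planned SE 0.22, half-width 0.435, HR 1.5, N = 100 and no dropout allowance (Sample size calculation); 1:1 allocation (Randomisation and blinding); two-sided 5% level (Statistical analysis); 25 weeks = 175 days (Treatment period and follow-up); median 99 days (Background).

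**Assumptions not in the article.** Exponential healing times; dropout of 10 to 20%, with half of the healings in those participants lost.

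**1. Reproduce the stated interval.** The interval is 1.5 × exp(±1.96 × SE).
- SE 0.22: half-width 0.431, interval (0.975, 2.309).
- Half-width 0.435: SE = 0.435/1.96 = 0.222, interval (0.971, 2.317).

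The stated figures agree with each other to rounding.

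**2. Healings implied.** With 1:1 allocation, SE² ≈ 4/D, so D ≈ 4/SE².
- 4/0.22² = 82.6 and 4/0.222² = 81.2, so about 81 to 83 observed healings.
- The source SE carries the same proportion: 4/0.105² = 363 events among an implied 100 × (0.22/0.105)² = 439 participants, or 83%. The article does not give the source trial's size.

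**3. Healings expected from the 99-day median.**
- Placebo: 1 − 2^(−175/99) = 0.706.
- Aspirin at HR 1.5: 1 − 2^(−1.5 × 175/99) = 0.841.
- Healings: 50 × 0.706 + 50 × 0.841 = 35.3 + 42.0 = 77.3.
- SE = √(1/35.3 + 1/42.0) = 0.228; interval (0.96, 2.35).
- A simulated Cox model under the same assumptions gives a mean SE of 0.231 and an interval of (0.95, 2.36).

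Read as a ceiling of 75 healings, the Background's statement on non-healing gives 2/√75 = 0.231 and (0.95, 2.36).

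**4. Add the assumed dropout.**
- 10%: 77.3 × 0.95 ≈ 73.5 healings; SE 0.228/√0.95 = 0.234; interval (0.95, 2.37).
- 20%: 77.3 × 0.90 ≈ 69.6 healings; SE 0.228/√0.90 = 0.241; interval (0.94, 2.40).
- Simulated Cox model with dropout spread over follow-up: 74 and 71 healings, SE 0.235 and 0.240.

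**5. Power at HR 1.5.** Power = Φ(ln 1.5 × √D/2 − 1.96).

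| Healings | Power |
|---|---|
| 81–83 (implied by the article) | 45% |
| 77 | 43% |
| 74 | 41% |
| 70 | 39% |

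**6. What dropout would demand.** If lost participants yield no healings at all, reaching 81.2 to 82.6 healings at 10% dropout needs 81.2/90 = 90% to 82.6/90 = 92% of those retained to heal. At 20% dropout it cannot be reached, since only 80 remain.

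**The case against.** The case for leaving the paragraph alone has real substance.

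- **The arithmetic is right.** Step 1 reproduces the stated figures. The issue is a planning assumption, not a miscalculation.
- **A reader might infer that the stated interval is a best case.** It is not. With 100 healings the SE would be 0.200 and the interval (1.01, 2.22), which is narrower and excludes 1.
- **A reader might infer that the figures require zero dropout.** They do not. With 81 to 83 healings, 17 to 19 participants may be unhealed or lost. If 0.105 was observed in the source trial, it already reflects attrition there. The article does not say so, however, and gives a different reason for making no allowance.
- **A reader might test a much slower healing rate, such as half of placebo ulcers healed by week 25.** The documents do not support that as their own figure: it implies a 175-day median against the 99 days cited. The remark about ulcers taking over 6 months is not quantified. The non-healing fraction has no time horizon, and the Abstract puts it at up to a quarter where the Background says more than a quarter. It is therefore only loose support for a ceiling of 75.
- **The gap is small.** An SE printed as 0.22 could be anything from 0.215 to 0.225, or about 86 down to 79 healings; 77 is just below. If the Abstract's 27-week maximum counted as time at risk, about 80 healings and (0.97, 2.33) would follow, although the last two weeks appear to serve for confirming healing.
- **The consequence is disclosed.** The article says the interval includes 1, states openly that dropout is not allowed for, and proposes pooling individual patient data. That pooled analysis would use the actual data, so the planning SE does not affect it.
- **An article condenses.** The absence of a healed fraction or of the source trial's size is not itself a fault.

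These points limit the size of the problem. They do not rescue the dropout sentence, which gives a reason that fails on its face, nor do they bring the implied 81 to 83 healings into line with the cited median.

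**Conclusion.** The point holds at minor severity. The stated SE of 0.22 rests on about 81 to 83 observed healings net of loss. The only healing speed the article quantifies gives about 77 at HR 1.5, and an assumed 10 to 20% dropout gives about 74 to 70. The lower confidence limit moves from 0.97 to between 0.96 and 0.94, the upper from 2.31 to between 2.35 and 2.40, and power from about 45% to between 43% and 39%. The conclusion that the interval includes 1 does not change.

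These figures assume exponential healing, the 99-day median for the placebo arm, 175 days at risk, and the approximation that SE depends only on event counts, ignoring covariate adjustment. The dropout rates are illustrative. The objection to the dropout rationale needs none of these assumptions: losses are censored, and measuring them does not replace the missing events.

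**What to change.** Rewrite the precision paragraph so that it starts from the expected number of healings by week 25, net of an explicit dropout assumption, and give SE, interval and power over a short range. For example, using SE = 2/√D at HR 1.5:

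- 80 healings: SE 0.224, interval about (0.97, 2.33), power about 44%.
- 70 healings: SE 0.239, interval about (0.94, 2.40), power about 40%.

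Delete the sentence that justifies making no dropout allowance. If the borrowed SE is thought to include attrition already, say that instead and give the source trial's healed fraction and follow-up.

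The cost is one paragraph and slightly less favourable figures. The recruitment target of 100 and the acknowledgement that the interval includes 1 both stand.
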